### Number of intervention sessions

The number of intervention sessions was determined based on previous studies that used EMDR therapy for chronic pain management. A systematic review on the effect of EMDR therapy on chronic pain showed that 1–12 sessions (average of 6 sessions) were used to treat chronic pain. Longer sessions were used in cases of longer-term chronic pain [31]. As a result, the number of treatment sessions for this study has been set at 6, which will be held twice a week. The duration of each session is 30–90 min; this is based on the participants’ willingness and convenience [41]. Given that some participants may respond to the intervention and achieve the target before completing all of the sessions, the intervention will be continued for one more session. Then it will be documented in the final report. No intervention will be performed for the control group, but they will be asked to report their routine strategies to relieve menstrual pain.

### Measures

In this research, four instruments will be used for data collection:

*The demographic characteristics questionnaire* will be used to collect demographic and reproductive characteristics, including age, menarche age, education level, field of study, every menstrual cycle (length of menstrual period and bleeding period), and medication/drug use history. This questionnaire has been developed on the basis of the objectives of the study and its validity will be examined by the content validity method.

*The VAS* will be used to evaluate the severity of dysmenorrhea pain. An Iranian systematic review confirmed the validity and reliability of VAS for evaluation of dysmenorrheal pain [42]. The VAS is a 100-mm line where the “0” end (0) means completely painless and the other end (10) means the most intense pain imaginable. The patient marks the severity of pain on the line. The simplicity makes it easy to use for the assessment of pain [43].

*SUD* is a self-reporting scale with a 0- to 10-point rating scale. Participants are asked to report their level of distress or anxiety based on SUD scale. A score of 0 indicates the absence of distress, and a score of 10 indicates the maximum level of distress [39]. This scale has been widely used by Iranian researchers and its validity and reliability have been confirmed in their studies [44–46].

*The VOC* shows the level of belief in positive or negative recognition. Similar to the SUD scale, it is self-reporting and represents an individual’s assessment of her or his own cognition. A 7-point rating scale ranging from 1 to 7 is used to evaluate, quantify, and indicate the participant’s self-recognition. A score of 1 means a lack of belief in that particular cognition, and a score of 7 means a full belief in it [39]. This scale has been widely used by Iranian researchers and its validity and reliability have been confirmed in their studies [44–46].

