### Intervention

EMDR therapy will be performed in the intervention group. The participants are expected to attend all scheduled interventions in which the EMDR therapy will be implemented to manage their distressing memories of severe pain due to dysmenorrhea. The expected outcome is that the level of subjective distress will be reduced and positive cognition will be reorganized [27]. The EMDR therapy consists of eight essential phases, and several steps may be performed during one session:

Phase 1

This includes taking the history of the unpleasant condition, designing the treatment protocol, and preparing and evaluating the participant. This helps the therapist to determine the specific target to achieve. To identify this target, participants will be asked to talk about their memories of the menstruation, dysmenorrhea, and menstruation-related complaints as well as the epicenter of the pain. Then they will be asked to specify the traumatic event which disturbed them the most.

Phase 2: Preparation

Prior to initiation of the intervention for the first time, therapeutic targets should be established. The procedure of EMDR therapy and its effects and safety should be explained to the participants. Their questions and concerns should be addressed.

Phase 3: Assessment

In this phase, the components of the therapeutic target should be identified. When the memory has been identified, the participant will be asked to select the image that best stands for that memory. Then the participant will be asked to choose a negative cognition that expresses the dysfunctional self-assessment related to the unpleasant condition. In this phase, negative cognition about dysmenorrhea will be identified and the participant will be asked to imagine the worst picture about their dysmenorrhea. Then they will be asked to choose a positive cognition to be used to replace the negative cognition during the installation phase. They are encouraged to imagine having a less painful menstruation as a positive cognition.

Phase 4: Desensitization

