This is the desensitization step that targets the thrilling feeling of the participant. In this phase, the participants will be asked to provide their pre-treatment Subjective Units of Anxiety or Distress Scale (SUD) and Validity of Cognition Scale (VOC) scores. Then eye movement sets will be used and the distressing memory of dysmenorrhea will be processed. At the end of the phase, the client reports their level of negative affect by using the SUD.

Phase 5: Installation

This phase focuses on cognitive rehabilitation and reconstruction and on strengthening the positive cognition to replace the negative cognition. In this phase, the researcher will try to install the positive cognition of menstruation without dysmenorrhea in the participant’s mind. The participants will be asked to provide their VOC scores.

Phase 6: Body scan

This phase assesses and evaluates the physical tensions. This step is also called the physical scan. After the positive cognition is installed, the participants will be asked to hold in their mind both the target event (dysmenorrhea) and the positive cognition (menstruation without dysmenorrhea) and then scan their own body mentally from top to bottom. Then they will be asked to identify any remaining discomfort in the form of body sensation.

Phase 7: Closure

The completion or final step consists of interactive reporting and is designed primarily to maintain the balance of the participant in the session and re-evaluate her at the end. In this phase, the participants will reach a state of emotional equilibrium. They will be informed of the possibility of having disturbing images, thoughts, or emotions between the sessions. This is a positive sign and they should not be concerned.

Phase 8: Re-evaluation

This is a reassessment step and its goal is to ensure that all relevant events have been processed [39, 40].

The EMDR therapy would be performed by one of the researchers (SV). She has been trained by a clinical psychotherapist to implement this type of therapy.

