### Primary outcome

The primary outcomes are the pain intensity, anxiety, or distress in patients with primary dysmenorrhea and their cognition of the dysmenorrhea.

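### The SUD primary outcome has no stated object or time point, and the only SUD ratings described are taken inside EMDR sessions that controls never attend

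*Protocol article*

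**What the plan says.** Primary outcome: "The primary outcomes are the pain intensity, anxiety, or distress in patients with primary dysmenorrhea and their cognition of the dysmenorrhea". Under Measures, the SUD is the instrument for distress. It is a self-report scale from 0 to 10 with anchors at no distress and maximum distress, introduced with "Participants are asked to report their level of distress or anxiety based on SUD scale". No object, recall period or assessment time is attached to it.

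The occasions on which the SUD is asked appear only under Intervention:

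- **Phase 1.** Each woman talks about her memories of menstruation and dysmenorrhea. "Then they will be asked to specify the traumatic event which disturbed them the most".
- **Phase 3.** "the participant will be asked to imagine the worst picture about their dysmenorrhea". She then picks a positive cognition and is encouraged to picture a less painful period.
- **Phase 4.** The score labelled pre-treatment is taken here: "In this phase, the participants will be asked to provide their pre-treatment Subjective Units of Anxiety or Distress Scale (SUD". Next, "Then eye movement sets will be used and the distressing memory of dysmenorrhea will be processed". Finally, "At the end of the phase, the client reports their level of negative affect by using the SUD".

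Controls receive no intervention and are asked only for their usual ways of relieving pain (Number of intervention sessions). Follow-up of both groups, one and two months after the final session, is stated for pain (Study procedure). The repeated-measures ANOVA is also stated for pain scores (Statistical analysis).

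**The concern.** An endpoint needs an object, a time and conditions of measurement that are the same in both arms. For the SUD the protocol supplies none of these under Measures or Primary outcome. What it does supply, under Intervention, is a pair of ratings that belong to the therapy itself.

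Two consequences follow if those ratings become trial data. First, the earlier score is taken after the woman has been asked to call up her worst picture of dysmenorrhea, and the later one after the eye-movement sets in the same phase. Part of any fall may be the settling of affect that the session itself evoked, rather than less distress from dysmenorrhea in the following cycles. Second, a control participant has no session and no target memory, so the same rating cannot be obtained from her. The distress aim is a between-group question, and it would be answered by a within-group change or by a comparison of two different kinds of rating.

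**Working it through.** **1. Does the point rest on a figure?** No. The sample size section gives an effect size of 0.25, power 0.80, alpha 0.05 and 82 evaluable women. Reading 0.25 as Cohen's f for a between-group repeated-measures test, and assuming 4 measurements with correlation 0.5 (the protocol states neither), the noncentrality is f²·N·m/(1+(m−1)·ρ) = 0.0625 × 82 × 4 / 2.5 = 8.2. Power is then 0.808, so 82 is reproduced. The section gives no SUD mean, SD or correlation, so it says nothing about the size of this problem.

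**2. VAS and SUD side by side.**

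| | VAS (pain) | SUD (distress) |
|---|---|---|
| Object | dysmenorrhea pain | not stated under Measures; a dysmenorrhea memory in Phase 4 |
| Before allocation | monthly for two months | none described |
| During therapy | none described | start and end of Phase 4 |
| After therapy, both groups | one and two months | none described |
| Control group | yes | none described |
| Analysis named | repeated-measures ANOVA | none named |

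**3. Order of events.** Worst picture (Phase 3); positive cognition and imagery of a milder period (Phase 3); SUD labelled pre-treatment (Phase 4); eye-movement sets; SUD as negative affect (end of Phase 4). The first SUD therefore follows target imagery, although not immediately after the worst picture. The text does not say how long after, because the phases may be spread over sessions. It also does not say whether the worst picture is held in mind at the second rating.

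**4. What comparison can be made?**

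- (a) Only Phase 4 scores exist: there is no control value, hence no between-group contrast.
- (b) Phase 4 gives the EMDR baseline or outcome and controls are rated outside sessions: a contrast exists, but the two arms are rated under different conditions.
- (c) Both arms are rated outside sessions with the same question: the contrast is sound, but this is not described and its question is not defined.

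**5. Illustration for case (b) only.** Assume no true effect, 44 per group, a two-sided 5% t-test on change, SD 2 to 3, pre-post correlation ρ = 0.5, and an EMDR baseline raised by a shift s through imagery, with every other score unprovoked. All of these except the 44 and the 5% are assumptions. Then d = s/(SD·√(2(1−ρ))) = s/SD, and the noncentrality is d·√(44/2).

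| Shift | SD 2 | SD 2.5 | SD 3 |
|---|---|---|---|
| 0.5 | 21% | 15% | 12% |
| 1 | 64% | 46% | 34% |
| 2 | 100% (99.6%) | 96% | 87% |

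For example, s = 1 and SD = 2.5 give d = 0.40 and noncentrality 0.40 × 4.69 = 1.88. The entries are the chance of a significant SUD difference against a nominal 5%. The spread from 12% to nearly 100% shows that the inputs, not the protocol, determine the answer.

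**The case against.** The best reply is that Measures describes a scale in generic terms and Phase 4 describes one use of it. That is incomplete, not contradictory. A reader might infer two opposing definitions, a general unprovoked state in one place and a memory rating in the other. The text does not support this: Measures never says general or unprovoked; it simply gives no object.

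Other stronger readings also fail.

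- A reader might call the first score provoked because it comes straight after the worst picture. The positive imagery in between and the unstated interval make that an inference.
- A reader might conclude that the SUD can fall with no link to dysmenorrhea. The chosen memory is restricted to menstruation and related complaints, so the rating remains tied to the condition.
- A reader might suspect that different memories are compared over the course, because Phase 8 says that "its goal is to ensure that all relevant events have been processed". Nothing states that scores for different memories will be compared.
- The protocol does not say that Phase 4 scores are the trial baseline or outcome, so the false-positive table describes a scenario, not the plan.

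It can also be said that an article may leave the exact question wording to a fuller document. That is fair for wording. It does not dispose of the point, because the article does describe when the SUD is asked, labels one of those scores pre-treatment, and places every one of them where controls cannot be rated.

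**Conclusion.** The point stands as a defect in how a primary outcome is fixed. Distress is a primary outcome and the SUD is its only instrument. Measures and Primary outcome give it no object or time, and the text, followed as written, yields only in-session process ratings from one arm. Such ratings cannot answer the between-group distress aim, and a fall in them may partly be short-term recovery from evoked affect.

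The conclusion is conditional in one respect: it bites if Phase 4 scores are used as the EMDR baseline or outcome. That use is inferred from their being the only SUD occasions described and from the pre-treatment label. The size of any bias cannot be obtained from the document, and the percentages above are illustrative only. The pain outcome and the sample size are unaffected. The change should be made; Trial status says recruitment had not begun, so a common baseline could still be set.

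**What to change.** Under Measures and Primary outcome, define the SUD outcome as one fixed written question on distress about menstrual pain, scored 0 to 10 and answered without an imagery exercise. Ask it in the same way in both groups before allocation and together with the VAS one and two months after the last session. Under Intervention, state that the Phase 4 SUD scores are therapy-process ratings, reported descriptively and used neither as baseline nor as outcome.

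The cost is a few lines of protocol text and one additional question at assessments already planned for the VAS. No visits, staff or participants are added, and the therapy is unchanged. The downside is that a fixed question asked outside the session will probably show a smaller apparent effect than the in-session score.

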### Primary outcome

The primary outcomes are the pain intensity, anxiety, or distress in patients with primary dysmenorrhea and their cognition of the dysmenorrhea.

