### Research aims and hypothesis

The hypothesis is that EMDR therapy can decrease the severity of pain or pain perception in patients with primary dysmenorrhea. The aims are to investigate the effects of EMDR therapy on the intensity of pain, distress level, and validity of cognition.

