### Study procedure

After obtaining permission from the human ethics committee at Qazvin University of Medical Sciences, registering it at the Iranian Clinical Trial Registration Center, and obtaining required permissions from university authorities, the researcher will visit the female dormitories at Qazvin University of Medical Sciences to invite potential participants for this study. There are four dormitories for female students at Qazvin University of Medical Sciences. The researchers will provide the information on the purpose of the research, type of intervention, and confidentiality arrangement for the research data. The participants will be asked to sign the written consent form before enrolling in the study. The researchers also ensure the participants that they can leave the study at any time and can benefit from commonly used palliative treatments whenever they are not willing to continue to participate or when they have severe pain and discomfort related to dysmenorrhea.

During recruitment, potential participants will be initially assessed for the pain intensity related to primary dysmenorrhea monthly for 2 months. Eligible individuals will be randomly assigned to EMDR therapy and control (no intervention) groups by a simple random blocking method with four blocks. EMDR therapy will be performed in the intervention group. The follow-up evaluation of dysmenorrhea pain will be performed in both groups at 1 and 2 months after the last treatment session. The flowchart of the research procedure is presented in Fig. 1.

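### SUD and VOC are named primary outcomes, but their only timed assessments are inside EMDR sessions, so a randomised comparison on them is not secured

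*Protocol article*

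**What the plan says.** The Primary outcome section reads: "The primary outcomes are the pain intensity, anxiety, or distress in patients with primary dysmenorrhea and their cognition of the dysmenorrhea". Measures ties distress or anxiety to the SUD (0 to 10) and cognition to the VOC (1 to 7). The section on research aims gives all three outcomes the same standing: "The aims are to investigate the effects of EMDR therapy on the intensity of pain, distress level, and validity of cognition".

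Timing for SUD and VOC appears only in the Intervention section. Both scores are requested before treatment starts in Phase 4. Later in Phase 4, "At the end of the phase, the client reports their level of negative affect by using the SUD". In Phase 5, "The participants will be asked to provide their VOC scores".

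For the comparator, Number of intervention sessions says: "No intervention will be performed for the control group, but they will be asked to report their routine strategies to relieve menstrual pain".

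The both-arm follow-up in Study procedure is: "The follow-up evaluation of dysmenorrhea pain will be performed in both groups at 1 and 2 months after the last treatment session". The Abstract likewise schedules pain intensity for both groups, at 1 and 2 months before and 1 and 2 months after the intervention. Statistical analysis describes a repeated-measures ANOVA comparing mean pain scores between groups, and names no other outcome.

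The Abstract and Measures also list SUD and VOC among the study's data-collection instruments. They give no time points and do not restrict the scales to one arm.

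**The concern.** In a randomised trial, the effect of EMDR on distress and cognition means a contrast between the arms. That needs the same measurement, of the same thing, at comparable times in both arms. The protocol sets this out for pain. For SUD and VOC it sets out only ratings given during therapy.

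If staff follow the text literally, these two primary outcomes yield changes within the EMDR arm only. Such a change mixes any treatment effect with time, regression to the mean and the demand of the session. The Intervention section itself expects therapy to reduce distress and reorganise cognition. The trial is unblinded (Blinding), and the researcher who delivers the therapy is also responsible for collecting the data (Intervention, Data management). Without controls, none of these influences can be separated from an effect of EMDR.

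**Working it through.** No numerical error is alleged, so the main check sets the sections side by side.

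| | Pain (VAS) | Distress (SUD) | Cognition (VOC) |
|---|---|---|---|
| Primary outcome (Primary outcome) | yes | yes | yes |
| Aim (Research aims and hypothesis) | yes | yes | yes |
| Listed as study instrument (Abstract, Measures) | yes | yes, no arm limit, no times | yes, no arm limit, no times |
| Timed assessment | 1 and 2 months before and after | EMDR Phase 4, start and end | EMDR Phase 4, start, and Phase 5 |
| Schedule stated for both arms (Abstract, Study procedure) | yes | none | none |
| Between-group analysis (Statistical analysis) | yes | none | none |

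1. All three outcomes are declared primary, but only one has a stated assessment time in the control arm.
2. The timed SUD and VOC ratings are tied to therapy steps. Controls have no sessions, so those time points do not exist for them.
3. The object being rated also comes from therapy. In Phase 3 the participant identifies the memory, the negative cognition and the positive cognition that Phases 4 and 5 then work on. Controls do not go through Phase 3. Even if they were handed the two scales, the protocol defines no memory or statement for them to rate.

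The sample size was checked as a side test of which outcome the trial was planned around. The inputs from Sample size calculation are an effect size of 0.25 (read as Cohen's f), alpha 0.05, power 0.80 and N = 82. The number of measurements m and their correlation ρ are not stated. For the between-group test in a repeated-measures ANOVA with two groups:

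λ = N × f² × m / (1 + (m − 1)ρ), with 1 and N − 2 degrees of freedom.

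With m = 4, matching the four pain time points, and ρ = 0.5 as an assumption:

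λ = 82 × 0.0625 × 4 / (1 + 3 × 0.5) = 20.5 / 2.5 = 8.2, giving power 0.808.

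N = 82 is also the smallest even total that reaches 0.80, so the plan's figure is reproduced. Other settings give:

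| m | ρ | N |
|---|---|---|
| 4 | 0.3 | 62 |
| 4 | 0.7 | 100 |
| 3 | 0.5 | 86 |
| 2 | 0.5 | 98 |
| 2 | 0.3 | 84 |
| 1 | – | 128 |

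The figure therefore fits the four-point pain schedule. Because m = 2 with ρ = 0.3 comes close, this is consistent with planning on pain but does not prove it. No schedule is stated for SUD or VOC, so the sample size cannot be tied to them.

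**The case against.** The strongest reply is that this is silence, and silence in a condensed article proves little. The Abstract and Measures present SUD and VOC as instruments of the whole study, and Measures speaks of participants in general as the people who report SUD. The aims imply a two-arm comparison. Nothing says controls will not be asked. The procedure flowchart (Fig. 1) and Additional file 1 are not shown, and a full protocol or statistical analysis plan may supply the missing schedule and analyses.

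Much of this stands, and it rules out three stronger readings:

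- A reader might infer that controls will have no SUD or VOC data and that no comparison is possible. The text leaves control-arm collection unspecified but does not exclude it.
- A reader might infer that in-session improvement would appear whatever happens to dysmenorrhea, and would be reported as success. The documents give no figure for this, and Statistical analysis describes a between-group comparison, with no separate within-arm test.
- A reader might infer from the control-group sentence that only controls report pain-relief use. That sentence describes the control condition. Secondary outcome does not limit pain relief to one arm, and the demographic questionnaire, also not limited, covers medication history.

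The absence of SUD and VOC from Statistical analysis is weak evidence by itself, since an unseen analysis plan could cover them.

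What does not stand is the claim that the article is merely silent. It states when SUD and VOC are taken, and places those times inside therapy. It states a both-arm schedule, and limits it to pain. The general statements in the Abstract and Measures give controls neither a time nor something to rate.

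**Conclusion.** The concern holds in a limited form. For two of the three named primary outcomes, the protocol states no control-arm assessment time and no item that controls could rate, so a randomised comparison is not secured as written. The count of two in three assumes that anxiety or distress is one outcome measured by the SUD and cognition is one measured by the VOC, as Measures indicates. The conclusion rests on the article text; a schedule in Fig. 1 or the full protocol that covers both arms would settle the timing, but the rateable item would still need to be defined. The matter should be resolved before enrolment, because a baseline rating that was not taken before randomisation cannot be recovered afterwards.

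**What to change.** State in Study procedure that SUD and VOC are collected in both arms, outside therapy sessions, at baseline before randomisation and at the same 1- and 2-month follow-ups as the VAS. Define a standard item for each scale that every participant can rate, for example distress about menstrual pain, and belief in one fixed positive statement about menstruation. Compare the arms on these scores. Describe the SUD and VOC ratings taken in Phases 4 and 5 as process measures in the EMDR arm only.

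If this is not done, stop naming SUD and VOC as primary outcomes and keep menstrual pain VAS as the primary.

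The cost is two short self-ratings added to a form that participants already complete, plus the work of writing the standardised items. The validation that Measures cites would need checking against the new wording. No additional assessment occasions are needed, since the VAS is already recorded before allocation and at both follow-ups. Trial status says recruitment has not begun, so the change can still be made for every participant.
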